### Interim analyses {21b}

ICIQ-SF and a 3-day bladder diary will be collected at the end of week 2 as interim analysis to make potential modifications for the planned sample size based on the accumulating data within the trial.

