### Active control group

Trained uro-physiotherapists will help the patients to initiate the PFMT program. At the beginning of the first session, the uro-physiotherapists will inform the patients of the history of PFMT and its benefits. Patients will be trained in a group of 6–8 patients. Before the training, clear goals for each session and the program as a whole will be given to all the patients. After each training session, the patient will fill out a treatment checklist and give suggestions related to the training. Uro-physiotherapists will then provide written/oral feedback for the patients on their improvement and concerns about their training. All the uro-physiotherapists will meet with the research team to ensure the consistency of the training protocol and discuss the concerns that may occur during the delivery of the training. The PFMT program meets the American College of Sports Medicine principles for prescribing exercise, including frequency, intensity, time, type, volume, and progression [20]. Patients in the active control group will receive PFMT twice per week for 5 weeks, making a total of 10 sessions. Every 2 sessions will be separated by at least 48 h. Each session lasts 50 min with a target of increasing pelvic floor muscle strength, power, endurance, and coordination in daily life context. The detailed training protocol will follow the Consensus on Exercise Reporting Template (CERT) [21]. It provides a direction for reporting exercise-related interventions regardless of exercise type and includes 16 items under 7 domains: what, who, how, where, when, dosage, tailoring, and compliance.

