### Outcomes {12}

The primary outcome of the study is the International Consultation on Incontinence Questionnaire–Short Form (ICIQ-SF) [27]. It is a widely used four-item questionnaire with full validation that assesses the voiding frequency, voiding volume, impact on quality of life, and the cause of leakage during the past 4 weeks. The total score of the questionnaire ranges from 0 to 21, with 0–7 representing mild UI, 8–12 representing moderate UI, and 13–21 representing severe UI.

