#### Sample size {14}

The present study intends to apply ICIQ-SF as the primary outcome. After calculation, a sample size of 44 in each group is able to provide 80% power to detect a within-between-group difference measured using ICIQ-SF at three time points, assuming a small effect size (Cohen’s *f*) of 0.125 and a two-sided significance level of 5%. Considering that there is a 20% dropout rate, the study will increase the sample size to 165 in total.

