### Oversight and monitoring

#### Composition of the coordinating center and trial steering committee {5d}

The two authors from the coordinating center will take full responsibility for conducting the intervention, scientific validity, and patient management. A report of the progress will also be submitted to the ethics review board of the coordinating center on a monthly basis. The trial steering group will review and provide guidance on subject recruitment, evaluation, and treatment to ensure consistency in all operations. All the authors will participate in periodic meetings to discuss the progress of the study and strategies to better manage the trial weekly.

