#### Composition of the data monitoring committee, its role, and reporting structure {21a}

The trial is going to be conducted in accordance with the Good Clinical Practices and Chinese regulations. The present study does not declare a data and safety monitoring board as electromagnetic stimulation and pelvic floor muscle training are both regarded as low risk and have been used routinely in patients who need medical care urgently.

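### The sample size may be changed on week-2 data, when group 2 has finished 10 of 10 sessions and the other two arms 4 of 10, and the review is not limited to pooled data

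*Protocol article*

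**What the plan says.** All references are to the Protocol article.

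- **Interim analyses {21b}** fixes the data, the time and the purpose: ICIQ-SF and the bladder diary "will be collected at the end of week 2 as interim analysis to make potential modifications for the planned sample size", with the change to rest on data accumulating in the trial. It does not say whether the data are pooled or split by arm.
- **Active control group:** "Patients in the active control group will receive PFMT twice per week for 5 weeks, making a total of 10 sessions". The Group 1 section gives the same schedule. The Group 2 section gives ten daily sessions.
- **Abstract, Methods/design:** the primary outcome is the change in ICIQ-SF after the ten sessions.
- **Sample size {14}:** 44 per group for 80% power on an effect "measured using ICIQ-SF at three time points", with Cohen's f of 0.125 and two-sided 5%; 165 in total after 20% dropout. The Abstract and {18a} put the time points at baseline, after the intervention (week 5) and 3 months.
- **Outcomes {12}:** the ICIQ-SF items cover "impact on quality of life, and the cause of leakage during the past 4 weeks".
- **Oversight:** {21a} states "The present study does not declare a data and safety monitoring board", and {23} repeats that there is no committee. Under {5d}, "The two authors from the coordinating center will take full responsibility for conducting the intervention". Under {16c}, allocation is revealed to participants and researchers.
- **Study setting {9}:** the outcome assessor and the data analyst are to be blinded.

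**The concern.** A sample-size review is useful only if it updates the quantities on which the size was set. Here those are the spread and within-patient correlation of ICIQ-SF over baseline, week 5 and 3 months, and dropout. Week 2 supplies none of the ICIQ-SF quantities.

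A week-2 comparison involving group 2 sets a finished course against 40% of one. The comparison of group 1 with control is balanced in sessions, but both are at 40% of the course. A larger or smaller trial chosen on such figures could be mis-sized in either direction.

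The wording also leaves arm comparisons open. If observed differences moved the sample size and the final test took no account of it, the type I error would rise. With an open-label design, a patient-reported primary outcome and no board, the text puts no explicit barrier around such a look.

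**Working it through.** **1. The plan's own figure.** Within-between interaction in repeated-measures ANOVA with k = 3 groups, m = 3 times and f = 0.125. The correlation ρ among repeated measures is not stated, so ρ = 0.5 and sphericity are assumed.

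- λ = N·m·f²/(1 − ρ) = 132 × 3 × 0.015625 / 0.5 = 12.375
- df1 = (k − 1)(m − 1) = 4; df2 = (N − k)(m − 1) = 129 × 2 = 258
- Power from the noncentral F at 5% = 0.808. N = 132, or 44 per group, is the smallest balanced size that reaches 80%.
- Dropout: 132 / 0.8 = 165.

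Both stated figures reproduce. The size depends strongly on ρ:

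| ρ | n per group for 80% | power at 44 per group |
|---|---|---|
| 0.3 | 61 | 0.645 |
| 0.4 | 52 | 0.722 |
| 0.5 | 44 | 0.808 |
| 0.6 | 35 | 0.895 |
| 0.7 | 27 | 0.966 |

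**2. Treatment received by the end of week 2.** Control and group 1: 2 per week × 2 weeks = 4 of 10. Group 2: ten daily sessions, so 10 of 10 by day 14.

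**3. Recall window.** Assume that baseline is taken immediately before treatment (day 0). The 28-day windows are:

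- baseline: day −28 to 0
- week 2: day −14 to 14
- week 5: day 7 to 35

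At week 2, 14 of the 28 days precede treatment. The baseline and week-2 windows share 14 days; the baseline and week-5 windows share none. A baseline to week-2 correlation is therefore likely to exceed the baseline to week-5 correlation. By the table, too high a ρ points to too small a trial. This direction is an inference, not something the article states, but it shows that pooling alone does not make week-2 scores suitable.

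**4. Type I error if arm differences were used.** The article gives no rule, so all of the following is assumed: one two-arm comparison, a look at 27 of 55 per arm, and new n per arm = 2(1.96 + 0.8416)²/d² with d the observed standardised week-2 difference. The new n is limited to between 55 and a cap (increase only) or between 27 and a cap (increase or decrease), with caps of 110, 165 and 275. The final z-test is unadjusted at two-sided 5%. Let r be the correlation between a patient's week-2 score and the final endpoint. Null simulation, 2,000,000 runs, results for the three caps in order:

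| r | increase only | increase or decrease |
|---|---|---|
| 0.3 | 5.1 / 5.1 / 5.1% | 5.1 / 5.2 / 5.2% |
| 0.5 | 5.2 / 5.4 / 5.4% | 5.4 / 5.5 / 5.6% |
| 0.7 | 5.4 / 5.6 / 5.8% | 5.8 / 6.0 / 6.2% |
| 1.0 | 6.0 / 6.4 / 6.7% | 6.8 / 7.2 / 7.5% |

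Repeat runs differ by about 0.1 percentage points. The row r = 1.0 treats the week-2 score as the endpoint itself, which it is not.

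**The case against.** **The text does not say that the review is unblinded.** This stands. It is unrestricted, not declared unblinded, and {9} blinds the data analyst. That is a real, partial safeguard. It does not settle the matter: {21b} does not invoke it, and an analyst who compares three masked arms still sees differences between them, which pooled data would not show.

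**A reader might infer that the treating team will see interim arm results.** No section says so. {5d} makes the two coordinating-centre authors responsible for delivering the intervention but does not mention interim data, and {16c} concerns allocation, not results.

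**A reader might infer a type I error of 6.0–7.5%, or even 9–10%.** The first range needs a week-2 score identical to the final endpoint, which contradicts the point that week 2 measures something else. The second also needs a rule tuned to maximise rejection and free to cut the sample size. Neither is supported.

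**Week-2 scores might enter the GEE as a fourth visit.** The article lists three time points and nothing adds week 2 to the model, so this is a matter for a clarifying sentence only.

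**The missing error control and maximum size could sit in an analysis plan not shown.** Agreed; they are not counted here. The week-2 timing and the absence of a board are fixed in this article.

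**The recall problem is not special to the interim and does not touch the 3-day diary.** Partly right. Recall dilutes all arms alike, and it would also affect group 2 if its primary assessment came straight after its ten sessions. The diary has no 4-week recall, but it too would compare 10 sessions with 4.

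**Conclusion.** The point holds. As written, {21b} bases a possible change of sample size on data from a time that is outside the calculation and at which the arms have had 10, 4 and 4 of their 10 sessions. The session counts follow directly from the schedules. The 14 of 28 pre-treatment recall days assume baseline immediately before treatment. The main harm is a wrongly sized trial; how wrong cannot be computed, because neither a rule nor a correlation is given.

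The type I error concern is secondary and conditional. It arises only if arm differences drive the change and the final test is unadjusted. On the assumed rules, two-sided 5% becomes about 5.0–5.2% at a correlation of 0.3, 5.2–5.6% at 0.5 and 5.4–6.2% at 0.7. The 6.0–7.6% seen across runs at a correlation of 1 is a bound, not an expectation. If the review is pooled and blinded, the inflation is negligible.

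**What to change.** Rewrite {21b} to state that:

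- any sample-size review uses only blinded data pooled over the three arms, on the quantities behind the calculation: the SD and within-patient correlation of ICIQ-SF at baseline and week 5, and dropout;
- no comparison between arms is made, with or without masked labels;
- week-2 ICIQ-SF and diary data are not used to change the sample size and stay outside the primary GEE model.

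The alternative is to delete the interim analysis.

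The cost is protocol wording. The review comes about 3 weeks later per participant (week 5 instead of week 2), and the early look at effect is lost.

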### Methods for additional analyses (e.g., subgroup analyses) {20b}

No subgroup analysis was planned due to the small sample size of the study.

### Methods in analysis to handle protocol non-adherence and any statistical methods to handle missing data {20c}

The main analysis of the study will adopt the intention-to-treat (ITT) method, in which all the patients will be included in the final analysis according to the random allocation regardless of the study completion. Also, generalized estimation equation (GEE) models will be used to analyze the outcomes collected at different time points. This approach could fit the outcomes at different time points so all the participants are allowed in the analysis, even if missing data exists. The study will report the rate of missing data, and the missing data will not be replaced.

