#### Criteria for discontinuing or modifying allocated interventions {11b}

Patients of the study are allowed to withdraw from the study at any time for any reason if they wish to do so without any consequences. The researchers of the study can also discontinue the participation if the participant is uncooperative and does not attend the study visits, and this patient will not be replaced by a new patient.

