#### Plans to promote participant retention and complete follow-up {18b}

Before and during the intervention, participants will be given extensive information related to the importance of electromagnetic and PFMT for UI. Participants are allowed to discontinue at any time point of the study without giving a reason. However, if possible, these participants will also be asked to provide the outcomes of the study at week 5 and follow-up. Questionnaires, bladder diary, and pelvic floor muscle function are routinely applied in urology outpatient and are characterized by efficiency and convenience.

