## Statistical methods

### Statistical methods for primary and secondary outcomes {20a}

The main analysis will follow the intent-to-treat principle with all the randomized patients included. The present study will keep the missing data and will not replace them. Normally distributed variables will be presented as mean (SD) values. Non-normally distributed continuous variables will be reported as medium values with interquartile ranges (25th–75th percentile), and percentages will be used for categorical variables. The Shapiro–Wilk test will be used to examine the normal distribution of the variables.

Baseline demographic data will be reported for all patients randomized to the three groups. These data include patients’ age, education level, employment, annual household income, and medical history (BMI, ever pregnant, cigarette smoking, and diabetes). Baseline data will be evaluated by *χ*
^2^ or Fisher’s exact for categorical variables, analysis of variance (ANOVA) for continuous variables, and the Kruskal–Wallis test for non-parametric variables.

Generalized estimation equation (GEE) models will be applied to analyze primary and secondary outcomes collected at different time points. Considering the potential effects of age, BMI, severity of UI, and other variables on the outcomes, subgroup analysis will be carried out to evaluate whether age (< / ≥  50 years), the severity of UI (ICIQ-SF < </ ≥  13 points), and BMI (< / ≥ 25 kg/m^2^) at baseline could have an impact on the effect of the treatment. In view of the fact that patients may not be able to complete all courses of the treatment due to various reasons during the treatment, we will also conduct per protocol analysis. Patients who have completed the original intervention as described above will be included.

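### GEE on observed data with no replacement is presented as keeping every randomised patient in the intention-to-treat analysis, but it is valid in general only under restrictive missingness, and outcome collection after staff-initiated discontinuation is not secured

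*Protocol article*

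**What the plan says.** Sections {20a} and {20c} of the protocol article fix the analysis. The model: "Generalized estimation equation (GEE) models will be applied to analyze primary and secondary outcomes collected at different time points". The population is intention-to-treat: "all the patients will be included in the final analysis according to the random allocation regardless of the study completion". Missing values: "The present study will keep the missing data and will not replace them", and again in {20c}, "The study will report the rate of missing data, and the missing data will not be replaced". The reason offered in {20c} is that GEE fits outcomes across time points "so all the participants are allowed in the analysis, even if missing data exists". Neither section states a missingness assumption, weighting or a working correlation.

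Other sections bear on how much will be missing and why:
- Sample size {14} plans for loss: "Considering that there is a 20% dropout rate".
- Section {11b}: "The researchers of the study can also discontinue the participation if the participant is uncooperative and does not attend the study visits".
- Section {18b}, after noting that participants may stop whenever they wish, adds: "if possible, these participants will also be asked to provide the outcomes of the study at week 5 and follow-up".
- Study setting {9} gives control and group 1 two sessions a week for 5 weeks, and group 2 ten consecutive days. Section {17a} calls the trial open-label, and {16c} reveals the allocation to participants and researchers.

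**The concern.** The protocol treats inclusion in a GEE data set as if it settled the missing-data question. It does not. Unweighted GEE uses only the responses that were observed. Its estimates are consistent in general only when missingness is completely random or depends on covariates in the model. A patient with a baseline score alone counts as included but carries essentially no information on the post-treatment difference.

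If patients leave for reasons linked to their scores, and those reasons differ by arm, part of the estimated arm difference reflects who stayed. Participants know their arm, the attendance burden differs between arms, and the primary outcome is self-reported, so this pattern is possible. Section {11b} lets researchers who know the allocation end the participation of uncooperative non-attenders, and nothing says that outcomes are still sought from those patients. That sits badly with an analysis of everyone regardless of completion.

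The matter is not simply left to an analysis plan. A plan that added imputation would contradict the protocol's own statement that missing data will not be replaced.

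**Working it through.** **1. The plan's own figures.** Inputs from {14}: f = 0.125, 44 per group (N = 132), three arms, three time points (m = 3), 5% two-sided, 80% power. Assumed because not stated: within-person correlation 0.5 and sphericity. For the within-between interaction:

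λ = f²·N·m/(1 − ρ) = 0.015625 × 132 × 3 / 0.5 = 12.375, with 4 and 258 degrees of freedom.

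Power is 0.808, which agrees with the stated 80%. Dropout: 132/0.80 = 165, or 55 per arm. The plan therefore allows for 165 − 132 = 33 patients lost.

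**2. What f = 0.125 means for group 2 versus control.** The protocol gives no arm difference. Assume equal steps d from control to group 1 to group 2, absent at baseline and the same at both later visits.
- Arm deviations −d, 0, d: mean square 2d²/3.
- Time deviations −2/3, 1/3, 1/3: mean square 2/9.
- f = d·√(2/3 × 2/9) = d·√(4/27) = 0.385d.
- d = 0.125/0.385 = 0.325 SD per step, so group 2 versus control is 2 × 0.325 = 0.65 SD.

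**3. Bias at week 5 under assumed dropout.** Large simulated samples, no true effect, correlation 0.5. The logit of dropout before week 5 is −1.75 + 1.2·s·(standardised baseline score), with s set by arm; this gives 15% to 20% dropout per arm. Entries are the group 2 minus control bias in SD.

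| s (control, group 1, group 2) | Independence, baseline as an outcome | Independence, baseline as a covariate |
|---|---|---|
| 1, 0, −1 (opposite) | 0.196 | 0.00 |
| 1, 0.5, 0 (graded) | 0.098 | 0.00 |
| 1, 1, 1 (same) | 0.00 | 0.00 |

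Against the matching 0.65 SD: 0.196/0.65 = 30% and 0.098/0.65 = 15%. Higher ICIQ-SF is worse, so these mechanisms work against group 2; reversing them would favour it by the same amount.

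**4. Working correlation.** In 150 trials of 55 per arm with the same mechanisms (Monte Carlo SE about 0.018), the bias for independence GEE / exchangeable GEE / mixed model was:
- opposite: 0.212 / 0.023 / 0.013
- graded: 0.091 / 0.002 / −0.001
- same: 0.019 / 0.021 / 0.021

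**5. Bias at 3 months.** When dropout follows the week-5 score, independence GEE with opposite-direction dropout gave 0.215, against 0.022 (exchangeable) and 0.019 (mixed model). Adding baseline as a covariate to the independence fit still leaves about 0.10 (opposite) and 0.05 (graded), because the driver of dropout is not in the model.

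**6. A second set of assumptions.** 600,000 simulated patients, SD 4, true difference −1.0 point, correlation 0.5, about 18% to 22% missing at 3 months:
- completely random missingness: bias about 0 for every working correlation;
- dropout on the week-5 score, opposite directions by arm: +0.64 to +0.65 (independence), +0.01 to +0.10 (exchangeable), +0.04 to +0.06 (unstructured);
- the same mechanism in all arms: +0.04 to +0.05 (independence), +0.01 otherwise;
- dropout on the unseen 3-month score itself, opposite directions: +0.88 to +1.30, whatever the working correlation.

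The last line is why a sensitivity analysis is needed as well as a different primary method.

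**The case against.** The strongest reply is that the bias comes from modelling choices the protocol does not make. It needs an independence working correlation and no baseline covariate. With baseline ICIQ-SF in the model the week-5 bias disappears, and exchangeable GEE stays close to the mixed model in the runs above. Working correlation, covariates and sensitivity analyses are commonly left to an analysis plan. This stands as a limit on the size of the problem. It does not rescue the reasoning in {20c}, which credits GEE as such. Nor can an analysis plan add imputation without departing from the protocol.

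Opposite-direction dropout is also an assumption. The protocol gives a single overall 20% and no reasons for leaving. This stands too: a reader might infer that differential dropout is likely, but the open-label design and unequal schedules show only that it is possible.

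A reader might set 0.20 SD against the 0.325 SD step and conclude that the bias could take up most of the effect. That mixes contrasts. The 0.325 SD is one step between adjacent arms, while the bias is for group 2 versus control, for which the same pattern gives 0.65 SD.

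On {11b}, the rule requires a patient to be both uncooperative and absent from visits, so many of these outcomes would be missing anyway, and {18b} does seek data after discontinuation. The remaining gap is narrower: {18b} speaks of participants who choose to stop, and only where possible.

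Finally, the sentence in {20c} is literally true, since a baseline-only patient can enter a GEE with baseline as one of the outcomes. The fault lies in relying on it as the answer to missing data.

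**Conclusion.** The point holds in a limited form. The protocol fixes an observed-data GEE, excludes replacement, and relies on a justification that does not secure the intention-to-treat comparison. Under assumed score-dependent dropout that differs by arm, with independence working correlation and no baseline covariate, the bias is about 0.10 to 0.20 SD for group 2 versus control. That is some 15% to 30% of the 0.65 SD implied under a linear arm pattern. It is near zero if dropout acts alike in all arms, if dropout depends only on baseline and baseline ICIQ-SF is a covariate, or if the working correlation is correct.

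The dropout mechanisms, the correlation of 0.5 and the linear arm pattern are assumptions, not protocol figures. The documents do not support saying that the trial's result will be biased, that GEE is unusable here, or that staff decisions will distort the comparison. They do support correcting the text, because the remedy is cheap and the primary estimate is exposed.

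**What to change.** 1. In {20a} and {20c}, state the missingness assumption and replace the no-replacement wording with a primary analysis that is valid when missingness depends on observed data. Two options are a likelihood-based mixed model for repeated measures with baseline ICIQ-SF and unstructured covariance, or baseline-adjusted GEE after multiple imputation by arm.
2. Add one sensitivity analysis for missingness that depends on unseen scores: a delta shift applied by arm.
3. Reconcile {11b} with {18b} and {20c}. State that ending participation in treatment does not end outcome collection, so that ICIQ-SF is sought at week 5 and 3 months from every randomised patient who has not withdrawn consent, including those stopped by staff.

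Cost: a few sentences, a little more analysis and some follow-up effort, with the sample size unchanged. The mixed model assumes approximate normality of a bounded 0–21 score; the imputation route keeps GEE for the analysis but needs an imputation model to be specified. Neither handles missingness that depends on unseen scores, which is the purpose of item 2.
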